### Interventions

2.6

All interventions in this study will be administered by professionally trained therapists. Tuina therapy will be performed by experienced Tuina practitioners, while core stability training will be guided by senior rehabilitation therapists. To ensure consistency of the interventions, both therapists will receive standardized training and pass a clinical trial operation assessment prior to the initiation of the study. All participants will receive individualized treatment three times per week (once every other day) for a total duration of 8 weeks. During the trial period, participants will be requested to refrain from receiving other treatments related to the study interventions, such as medications, acupuncture, or physical therapy. Participants who receive prohibited concomitant treatments will be withdrawn from the intervention but retained for intention-to-treat analysis. If additional treatments are deemed medically necessary, the trial will be terminated for that participant, and the relevant information will be documented in the case report form (CRF).

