#### Withdrawal criteria

2.2.3

Failure to complete the treatment according to the study protocol after enrollment.Poor compliance during the trial, including modification of the treatment protocol or receipt of other related therapies.Withdrawal from the study at the participant's request or termination of participation during the trial.

**Note:** Participants who withdraw from the intervention will still be encouraged to complete follow-up assessments whenever possible. All randomized participants will be included in the intention-to-treat analysis regardless of adherence.

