#### Termination criteria

2.2.4

The participant experiences serious adverse events related to the treatment intervention.Severe complications or significant deterioration of the disease occur during the study period.The investigator determines that the participant meets the criteria for trial termination according to the standard operating procedures, and the intervention should be stopped immediately.

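### Section 2.6 ends the trial, not only the treatment, for a participant who medically needs other care; read literally, this stops outcome collection that Section 2.2.3 means to continue

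*Protocol article*

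**What the plan says.** All references are to the protocol article.

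- **Section 2.6, Interventions.** Participants are asked to "refrain from receiving other treatments related to the study interventions, such as medications, acupuncture, or physical therapy". Two consequences follow in adjacent sentences. For prohibited treatment: "Participants who receive prohibited concomitant treatments will be withdrawn from the intervention but retained for intention-to-treat analysis". For treatment that is medically needed: "If additional treatments are deemed medically necessary, the trial will be terminated for that participant". The second sentence adds only that the event is recorded in the case report form.
- **Section 2.2.3, Withdrawal criteria.** The list includes "receipt of other related therapies", under poor compliance, and "termination of participation during the trial". The note below the list says: "Participants who withdraw from the intervention will still be encouraged to complete follow-up assessments whenever possible". It goes on: "All randomized participants will be included in the intention-to-treat analysis regardless of adherence".
- **Section 2.2.4, Termination criteria.** One criterion is that the investigator finds that the participant "meets the criteria for trial termination according to the standard operating procedures, and the intervention should be stopped immediately".
- **Section 2.11, Statistical analysis.** Efficacy is analysed in all randomized participants, with multiple imputation under missing-at-random for missing values.

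**The concern.** Section 2.6 contrasts leaving the intervention with ending the trial, and it attaches ITT retention only to the first. Staff who read the two sentences together could reasonably take the second as a fuller exit, after which no further visits are made. Medication is named among the treatments to avoid, so a participant given analgesia on medical grounds fits both sentences, and nothing says which prevails.

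The people affected are those judged to need more treatment. Some will have an unrelated illness, but others may need it because their back or leg symptoms have worsened. If their assessments stop, the gaps may be related to outcome. Imputation then relies on an assumption that the reason for stopping puts under strain, and values that were never collected cannot be recovered by any analysis.

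**Working it through.** The point rests on wording, so the check sets the rules side by side and then counts what one participant would lose.

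**1. What each rule ends, and what it says about follow-up**

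| Section | Trigger | What ends | Follow-up assessments | ITT status |
|---|---|---|---|---|
| 2.6, first rule | Prohibited treatment received | Intervention | Not stated here; the 2.2.3 note applies | Retained |
| 2.6, second rule | Additional treatment medically necessary | The trial, for that participant | Not stated | Not stated here; 2.2.3 and 2.11 retain |
| 2.2.3, list and note | Includes other related therapies and terminated participation | Note names withdrawal from the intervention | Encouraged | Retained |
| 2.2.4 | Related serious adverse event, deterioration, or investigator decision | Intervention | Not stated | Not stated here; 2.2.3 and 2.11 retain |

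**2. Do the two rules in Section 2.6 overlap?** Yes. Medication, acupuncture and physical therapy are all on the list of treatments to avoid, and any of them could also be medically necessary.

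**3. Does the rest of the article settle the meaning?** Only in part.
- Section 2.2.4 points to the milder meaning, because it ties trial termination to stopping the intervention.
- Section 2.7.3 (Adverse events) speaks of terminating the trial for safety, apparently meaning the study as a whole, so the phrase has no single sense.
- The note in Section 2.2.3 sits directly below a list that includes terminated participation, which suggests that these participants are meant to be followed. Its wording, however, covers only those who withdraw from the intervention.
- Sections 2.2.3 and 2.11 fix who is analysed. They do not fix whether a terminated participant is measured.

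**4. Values lost per participant if assessments end at termination.** Inputs are the schedules in Sections 2.1, 2.7 and 2.7.1.1. The primary transversus abdominis activation ratio is measured at baseline and after the intervention (week 8), which gives 1 post-baseline value. VAS and ODI are measured at baseline, week 8 and 1 month after the intervention, which gives 2 post-baseline values each.

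| Time of termination | Primary values lost | VAS values lost | ODI values lost |
|---|---|---|---|
| Before week 8 | 1 of 1 | 2 of 2 | 2 of 2 |
| After week 8, before the 1-month visit | 0 of 1 | 1 of 2 | 1 of 2 |

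The second row assumes that the Section 2.6 rule also runs during the follow-up month. The article does not define the trial period. If the rule does run then, no intervention is left to stop, so termination could affect only the remaining VAS and ODI assessments.

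**5. Relation to the sample size.** Section 2.5 reproduces. A two-sample t-test with d = 0.78, two-sided alpha 0.05 and power 0.80 gives 26.80, so 27 per group. Then 27 / (1 − 0.15) = 31.8, so 32 per group and 3 × 32 = 96 in total. The 15% allowance covers lost numbers, but it does not address bias from losses that are related to outcome. The documents give no rate of medically necessary treatment, so neither a power loss nor a bias can be calculated.

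**The case against.** The strongest reply is that the milder meaning is the natural one. Section 2.2.4 is the only place that says what termination means for a participant, and there it means stopping the intervention. Section 2.6 never says that assessments end or that the participant leaves the analysis. Section 2.2.3 puts other therapies and terminated participation under the same heading as the follow-up note. The two sentences in Section 2.6 may also have different triggers: a compliance breach in one and a clinical decision in the other. Finally, the article condenses a fuller protocol and refers to operating procedures that are not shown, so its silence on assessments after termination is not in itself a fault.

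Much of this stands. A reader might infer that Section 2.6 contradicts both Section 2.2.3 and Section 2.2.4. The documents do not support that: Section 2.2.4 is not contradicted at all, and Section 2.2.3 only on the literal reading. A reader might also infer that these participants are dropped from the analysis. They are not, because Sections 2.2.3 and 2.11 keep all randomized participants.

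The reply does not remove the stated difference between two adjacent operative rules that can apply to the same event. This is wording that staff act on at the visit, not a detail that an analysis plan could settle later.

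**Conclusion.** The point holds as an ambiguity with a real risk to data collection. The second rule in Section 2.6, taken literally, ends outcome collection and is then inconsistent with the follow-up and ITT intent of Section 2.2.3. The likely intention is that these participants are followed, so the loss is a risk and not a certainty.

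The harm would be avoidable missing data: for each affected participant, the single post-baseline primary value if termination comes before week 8, or one of two VAS and ODI values if it comes later. This assumes that assessments stop at termination and, for the later case, that the rule applies during the follow-up month. That the missingness is related to outcome is plausible but not shown. No overall bias or loss of power can be stated, because the article gives neither a termination rate nor outcomes after termination. The change is worth making because it is small and the lost values could not be restored.

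**What to change.** Replace the second rule in Section 2.6 with wording to this effect: where additional treatment is medically necessary, the study intervention is stopped for that participant; the scheduled week-8 assessments and the 1-month VAS and ODI go ahead if the participant consents; and the observed values enter the ITT analysis. Extend the note in Section 2.2.3 so that it expressly covers participants terminated under Sections 2.2.4 and 2.6.

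Clinical management does not change, and the needed treatment is still given and recorded. The cost is one reworded sentence, one extended note, and a few already scheduled visits for participants who are off treatment. Section 2.1 plans recruitment until 1 November 2027, so a change made during recruitment would still protect data from participants not yet assessed.

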#### Tuina group

2.6.1

The Tuina intervention comprised three standardized procedures targeting the lumbar–abdominal region. Firstly, all participants received standardized lumbar spine health education prior to the intervention. Subsequently, the Tuina procedures were performed with the participant in a supine position, with the hips and knees flexed.The procedures were carried out in the order of A–C (Figure 2), including rubbing, pushing, and acupressure techniques applied at predefined acupoints, namely Mingmen (DU4), Zhangmen (LR13), Daimai (GB26), Shenque (CV8), Wushu (GB27), and Weidao (GB28). The Tuina techniques and acupoint selection were based on a standardized national textbook (32). Each procedure was performed for approximately 3–6 min, and the three procedures constituted one complete session, lasting about 20 min. The manipulation intensity was standardized to achieve moderate pressure, defined as patient tolerance without pain. All procedures were conducted by trained practitioners. Treatments were administered three times per week for 8 weeks. The anatomical locations of the acupoints are shown in (Figure 3).

**Figure 2 F2:**
[figure not shown]
Tuina techniques. **(A)** Rubbing; **(B)** Pushing; **(C)** Pressing.

**Figure 3 F3:**
[figure not shown]
Locations of the acupoints. DU4 (Mingmen), LR13 (Zhangmen), GB26 (Daimai), CV8 (Shenque), GB27 (Wushu), and GB28 (Weidao).

#### Core stability training group

2.6.2

The CST protocol was developed based on established core stabilization principles and evidence-based recommendations for the management of chronic low back pain and LDH (6, 33). Specifically, the program was designed to progress from diaphragmatic breathing to quadruped contralateral limb extension and standing anti-rotation exercises. The exercise progression was informed by evidence supporting the role of breathing control, deep trunk muscle activation, and progressively challenging stabilization tasks in core stability training (34–36). The selected exercises were intended to facilitate coordinated activation of the transversus abdominis, multifidus, and related trunk musculature while maintaining safety and feasibility for patients with LDH. Firstly, all participants received standardized lumbar spine health education prior to the intervention. Subsequently, the exercises were performed under the supervision of a rehabilitation therapist. The exercises were carried out in the order of A–D (Figure 4), including diaphragmatic breathing training in the supine position, quadruped contralateral limb extension (bird-dog exercise), standing trunk rotation with elastic resistance, and balance training on an unstable surface. Each exercise was performed for three sets, with 10–15 repetitions or maintained for 6–10 s or approximately 1 min, depending on the specific task. A rest interval of 30–60 s was provided between sets and exercises to minimize fatigue. The total duration of each training session was approximately 20 min. Exercise intensity was adjusted according to participant tolerance to maintain a moderate level of exertion without exacerbating pain. Treatments were administered three times per week for 8 weeks.

**Figure 4 F4:**
[figure not shown]
Core stability training procedures. **(A)** Diaphragmatic breathing; **(B)** Bird-dog exercise; **(C)** Trunk rotation; **(D)** Standing on a balance pad.

#### Combined Tuina and core stability training group

2.6.3

Firstly, all participants received the same standardized lumbar spine health education as described for the other two groups. Subsequently, the combined intervention consisted of sequential Tuina therapy followed by core stability training, as described above. The Tuina procedure was performed first, followed immediately by the core stability training within the same session. The total duration of each session was approximately 40 min. Treatments were administered three times per week for 8 weeks. The difference in intervention duration between groups will be treated as a potential confounding factor and will be included as a covariate in the linear mixed-effects models to control for its potential influence on the outcomes.

### Outcomes

2.7

The efficacy evaluation in this study will focus on the primary and secondary outcome measures assessed at baseline and immediately after the intervention. In addition, selected clinical outcomes, including pain intensity and functional status, will be reassessed at the 1-month follow-up using the VAS and ODI to evaluate the persistence of treatment effects. Follow-up assessments will be conducted by independent outcome assessors who are blinded to group allocation.All outcome assessments will be conducted by independent researchers who are blinded to group allocation and are not involved in other aspects of the study. The schedule of enrolment, interventions, and assessments is presented in (Figure 5).

**Figure 5 F5:**
[figure not shown]
SPIRIT schedule. Enrollment, Intervention, and Assessment Schedule. CST, Core stability training group; MSK-US, Musculoskeletal ultrasound; MRI, Magnetic Resonance Imaging; VAS, Visual Analog Scale; ODI, Oswestry Disability Index; JOA, Japanese Orthopedic Association; SF-36, Short Form-36 Health Survey; PBU, Pressure Biofeedback Unit.

#### Primary outcome

2.7.1

The primary outcome is the muscle activation ratio of the transversus abdominis (TrA) assessed by musculoskeletal ultrasound, which reflects the neuromuscular control capacity of the deep core musculature. The muscle activation ratio is calculated as follows:

$$\begin{array}{l} \text{Activation ratio}=\frac{\text{muscle thickness duringcontraction}}{\text{muscle thickness at rest}} \end{array}$$

This measure has been widely used as an indicator of deep core muscle activation.

##### Musculoskeletal ultrasound assessment

2.7.1.1

Before and after the intervention, musculoskeletal ultrasound examinations will be performed using a Siemens Sequoia Silver ultrasound system (probe frequency: 5–12 MHz). The external oblique (EO), internal oblique (IO), transversus abdominis (TrA), and lumbar multifidus muscle (LMM) will be assessed in both groups. For EO, IO, and TrA measurements, the probe will be positioned at the level of the umbilicus along the mid-axillary line. The LMM will be located approximately 2 cm lateral to the L4 spinous process. Muscle thickness will be measured under standardized tasks: active straight-leg raising of the right lower limb in the supine position will be used for EO, IO, and TrA assessment, while single-leg standing on the left lower limb in the upright position will be used for LMM assessment. For each muscle, thickness will be measured three times at rest, at the end of standardized inspiration, and at the end of standardized expiration, and the mean value will be recorded. The muscle activation ratio will be calculated as the ratio of muscle thickness during contraction to that at rest. All measurements will be performed by an experienced sonographer. A subset of measurements will be repeated to assess intra-rater reliability.

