Current clinical practice guidelines recommend Tuina therapy and exercise-based rehabilitation as important nonsurgical interventions for LDH (6, 11). Tuina, a traditional manual therapy, has been shown to relieve pain and improve functional outcomes, potentially through mechanisms such as enhancing local circulation, reducing inflammation, and modulating neural activity (12). The Tuina protocol applied in this study primarily targets the Dai meridian region, which anatomically corresponds to the lumbar–abdominal musculature and thoracolumbar fascia. Acupoints such as Daimai (GB26), Wushu (GB27), and Weidao (GB28) are anatomically located along the lateral abdominal wall, corresponding to the external oblique, internal oblique, and transversus abdominis muscle layers. These points have been widely selected in clinical and experimental studies based on their relevance to abdominal musculature and their role in modulating lumbar stability and core function (13).Previous studies from our research group have demonstrated that abdominal Tuina can increase transversus abdominis thickness and improve lumbar function (14, 15). However, existing evidence suggests that while Tuina is effective in alleviating pain and improving physical function, its effects are primarily limited to symptomatic relief, with insufficient influence on deep muscle activation and neuromuscular control, which are essential for long-term spinal stability (9, 16).

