#### Objective outcomes

2.4.1

(Musculoskeletal ultrasound, MRI, X-ray, and pressure biofeedback unit) will be assessed by independent researchers who are blinded to group allocation and not involved in the intervention delivery.

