However, several limitations should be acknowledged. This is a single-center study with a relatively small sample size, which may limit generalizability. Blinding of participants and therapists was not feasible due to the nature of the interventions, which may introduce performance bias and expectation effects. Specifically, patient-reported outcomes (VAS, ODI, JOA, and SF-36) may be influenced by participants' perceptions and treatment expectations. To mitigate these biases, objective outcome measures—including musculoskeletal ultrasound, MRI, X-ray, and pressure biofeedback—will be assessed by independent evaluators blinded to group allocation, and statistical analyses will be conducted by investigators blinded to group allocation. Certain measurements, particularly ultrasound assessments, may still be subject to operator-dependent variability (44). Some mechanistic inferences rely on prior literature rather than direct measurement, and the absence of a sham or placebo control may further introduce expectation-related effects. The combined intervention group received twice the total intervention duration compared to monotherapy groups (20 vs. 40 min per session), although intervention duration will be included as a covariate, residual confounding cannot be entirely excluded. The upper age limit of 55 years restricts generalizability to older adults with LDH, and despite standardized training, some operator-dependent variability in Tuina procedures may remain. Future multicenter studies with larger sample sizes, longer follow-up periods, and time-matched control designs are warranted to confirm these findings and isolate the specific effects of the combined intervention. Overall, this study is expected to provide preliminary evidence and methodological guidance for integrating Tuina and core stability training in LDH management.

If proven effective, this combined approach may provide a practical and scalable rehabilitation strategy for patients with LDH in clinical settings.

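### The primary outcome's blind rests on coding and assessor independence, and neither prevents the sonographer from learning the arm at the scan

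*Protocol article*

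**What the plan says.** Section 2.7.1.1 (Musculoskeletal ultrasound assessment) describes the primary measurement. For the abdominal muscles "the probe will be positioned at the level of the umbilicus along the mid-axillary line". It adds "Muscle thickness will be measured under standardized tasks" and "All measurements will be performed by an experienced sonographer". It does not say when the thickness is read, or whether images are stored.

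Section 2.6.1 (Tuina group) describes the treatment as "including rubbing, pushing, and acupressure techniques applied at predefined acupoints", and the six points named include GB26, GB27 and GB28. The Introduction says that these three "are anatomically located along the lateral abdominal wall, corresponding to the external oblique, internal oblique, and transversus abdominis muscle layers". On intensity, section 2.6.1 states: "The manipulation intensity was standardized to achieve moderate pressure, defined as patient tolerance without pain".

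On blinding, section 2.4 says that allocation is coded and that participants and therapists cannot be blinded. Section 2.4.1 says that the objective outcomes "will be assessed by independent researchers who are blinded to group allocation and not involved in the intervention delivery". The Discussion presents these blinded objective measures, ultrasound first, as the mitigation for unblinded participants and therapists. It then concedes: "Certain measurements, particularly ultrasound assessments, may still be subject to operator-dependent variability".

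Two further places matter. Section 2.7.3 lists abrasion and bruising of the skin caused by Tuina among the adverse events to be recorded. Section 2.10 has outcome assessors fill in all case report forms, and names adverse events and ultrasound results among their contents.

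**The concern.** Coding protects the analyst, and independence keeps therapists from measuring. Neither protects a sonographer who has the participant and the treated region in view. There are three routes to unmasking:

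- **Sight.** A mark on the abdominal wall points to a Tuina-containing arm.
- **Speech.** The participant knows the arm and performs tasks in front of the sonographer.
- **Records.** If the assessor who enters ultrasound results also completes the adverse-event form, an entry for skin damage from Tuina reveals a Tuina-containing arm.

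At stake is the protection that the Discussion relies on. The outcome is a ratio of two small thicknesses, so a slight shift in reading changes it. The limitations mention operator dependence but not unmasking at the scan.

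**Working it through.** **1. Which arms each route can separate**

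| Route | Combined vs core training | Combined vs Tuina |
|---|---|---|
| Visible mark on the abdominal wall | Possible | No, both arms receive Tuina |
| Adverse-event entry for skin damage from Tuina | Possible | No |
| Participant mentions treatment | Possible | Possible |

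The trial asks whether the combination beats either therapy alone. Marks and records bear on one of those two comparisons, disclosure on both. Only the post-treatment scan is exposed, because Tuina has not begun at baseline.

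**2. The planned effect, as a yardstick**

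Inputs from section 2.5: effect size 0.78 (taken as Cohen's d), two-sided alpha 0.05, power 0.80, 15% dropout.

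- Normal approximation: n = 2 × (1.96 + 0.84)² / 0.78² = 25.8, so 26 per group.
- Two-sample t-test: 26.80, so 27 per group (power 0.803 at 27). This matches the plan.
- Dropout: 27 / 0.85 = 31.8, so 32 per group and 96 in total. This also matches.

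**3. Bias from visible marks alone (illustration)**

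The documents give none of the following inputs, so all are assumptions: 5% to 20% of Tuina recipients with visible marks; resting thickness 3.0 mm and contracted 4.5 mm; a 0.1 mm shift in the contracted reading when the arm is known; SD of the ratio 0.25.

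- Participants receiving Tuina: 2 × 32 = 64. Marked: 64 × 0.05 = 3.2 to 64 × 0.20 = 12.8, about 3 to 13 over both arms.
- In the combined arm alone: 32 × 0.05 = 1.6 to 32 × 0.20 = 6.4, about 2 to 6.
- Shift in one affected participant: 4.6/3.0 − 4.5/3.0 = 0.033; 0.033 / 0.25 = 0.13 SD.
- Shift in the arm mean: 0.13 × 0.05 = 0.0065 to 0.13 × 0.20 = 0.026 SD.
- As a share of the planned effect: 0.0065 / 0.78 = 0.8% to 0.026 / 0.78 = 3.3%.

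**4. If unmasking were widespread (illustration)**

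Disclosure has no natural ceiling. If every participant in one arm were unmasked and read with the same 0.13 SD shift, the arm mean would move by 0.13 SD, or 0.13 / 0.78 = 17% of the planned effect. The table gives rejection rates of a single two-sample t-test at nominal 5% when there is no true effect, for a range of shifts between two arms. The planned Bonferroni correction is ignored.

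| Shift between arms (SD) | Share of 0.78 | 27 per group | 32 per group |
|---|---|---|---|
| 0.1 | 13% | 6.5% | 6.8% |
| 0.2 | 26% | 11% | 12% |
| 0.3 | 38% | 19% | 22% |

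Nothing in the documents says where in this range, if anywhere, the trial would fall.

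**The case against.** The strongest reply is that nothing here contradicts the text. The article claims assessors who are blinded, independent and trained. Image-reading workflow and non-disclosure instructions are operational details that a full protocol or manual may hold. That stands: this is not an error in the document, and the blind may be better protected than the article shows. But the article does describe its blinding measures and its scan procedure, and the measures described do not reach the routes above. A stated method can be improved even where it contradicts nothing.

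A reader might also infer more than the documents support:

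- **That thickness is read live, from frames picked by hand.** Section 2.7.1.1 says who measures, not when or from what.
- **That the scan follows a Tuina session by minutes, with the skin still red.** Section 2.7 does place the assessment directly after the intervention, but it contrasts this with the 1-month follow-up, and section 2.1 gives the time point as the end of the 8 weeks. It names a visit.
- **That marks are expected at the probe site.** Section 2.7.3 lists possible events without a body site or a rate. Tuina is also applied at points other than GB26 to GB28, and pressure is kept below pain.
- **That 0.13 SD is the bias in the trial.** It is an assumed shift in one participant. Spread over an arm at the assumed mark rates it almost vanishes.

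Finally, disclosure is a risk in any trial with unblinded participants. That is true, and it is why later measurement from coded images is useful here.

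**Conclusion.** The point holds as a cheap improvement to the primary measurement. It does not show that the blind fails. The treated region and the scanned region overlap, participants know their arm, and outcome assessors complete forms that can name Tuina injuries. Coding and independence leave these routes open.

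The size is unknown. Through marks alone it is probably small, about 1% to 3% of the planned effect under the assumed rates, and confined to comparisons with core training alone. Disclosure could do more and could reach both key comparisons, but the documents give no basis for a figure. Two facts could shrink the point further: that images are already stored and read offline, or that the person who measures ultrasound does not handle adverse-event forms. The article states neither.

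**What to change.** - **Section 2.7.1.1:** save all rest and contraction frames under a code, following a fixed acquisition rule. The same sonographer measures thickness later, in random order, without arm, visit or participant identity. If this is already the practice, one sentence saying so is enough.
- **Section 2.7.1.1:** instruct participants before each scan not to mention their treatment.
- **Section 2.10:** have adverse events recorded by existing study staff other than the person who measures the ultrasound. Section 2.8.1 keeps therapists out of data collection, so this falls to the research team, which section 2.8.3 already charges with monitoring participants.

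The cost is file handling, a code list and a short delay before results are entered, for at most 96 × 2 = 192 scan visits. No additional reader, visit or procedure is needed. One limit remains: frames are still acquired and selected at the visit, so that step is only partly masked, and the fixed acquisition rule reduces this without removing it.
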